## 11 STATISTICAL METHOD

### 11.1 ANALYSIS PLAN

**Data Analysis.** Descriptive statistics will be utilised to report on the baseline characteristics of the total study cohort and each subgroup, as well as by site. The primary outcome measure investigating length of mechanical ventilation will be analysed using a Mann-Whitney test (assuming the data is non-normally distributed). Analysis of secondary outcomes includes both comparisons of measurements and proportions, using confidence intervals of differences as the major method of presentation where possible, otherwise standard techniques such as Mann-Whitney U tests, t-tests and chi-squared tests will be utilised. All analyses will be by intention-to-treat. Statistical significance will be set at the 0.05 level for the primary outcomes. Post-hoc power analyses may be undertaken to determine if results found in sub-group analyses are reliable.

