### 11.2 SAMPLE SIZE

**Sample Size.** Table 2 reports the pilot data, which supports the sample size calculation. Sample size calculations were updated based on individual patient level data from the pilot study to take the distribution of ventilator free days into account. The pilot study showed an approximate 66 hours (0.33 SD) reduction in ventilator-free days (VFD) associated with the study intervention [26]. Based on the primary outcome measure VFD, 1,320 patients (660 per group) would be required to demonstrate a significant increase in VFD assuming a minimally clinically significant small effect size (0.2 SD), 90% power, two-sided alpha level of significance of 5%, 10% withdrawals, and 15% increase in sample size to account for a non-normal distribution of VFD.

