## **Sample size**

Pilot study data demonstrated a 66 hour (0.33 SD) reduction in VFDs associated with the study intervention [26]. Assuming a minimally clinically significant small effect size (0.2 SD), 90% power, two-sided alpha level of significance of 5%, 10% withdrawals, and 15% increase in sample size to account for a non-normal distribution of VFD, 1,320 patients are required (660 per group).

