## **Statistical analysis**

### *Statistical analysis principles*

- Analyses will be conducted based on the intention-to-treat principle. Specifically, patients who are eligible, who do not meet any exclusion criteria and who undergo randomisation will be analysed based on the treatment group they were allocated to, independent of the compliance with the treatment delivered.
- Participants who had more than one surgery before their second birthday will only have data related to their first surgery for which study consent was available analysed.
- Statistical tests will be two-sided applying a statistical significance level of 0.05. As we are not correcting for multiplicity when comparing secondary or other outcomes, such results will be considered exploratory and will be reported as point estimates with 95% confidence intervals (CIs).
- If there is missing data for the primary outcome measure for any participants, imputation methods will be used.
- Continuous variables will be assessed for normality; this will be undertaken using visual inspection of histograms and Q-Q plots.
- Standard descriptive statistics will be used when summarising variables; frequencies (percentages) for discrete variables, mean and standard deviation (SD) for continuous

variables, or, if continuous variables are non-normally distributed, median with interquartile range (IQR).

- This analysis plan and the primary manuscript will only include analyses up to 28 days. We will present analyses of postoperative delirium, health care costs, inflammatory markers and long-term outcomes (12 months and later post procedure) separately.
- Pre-planned subgroup analyses will be performed including the pre-defined study strata; these will be executed regardless of any potential treatment effect on the primary or secondary outcomes in the main cohort.
- To ensure transparency and reproducibility, the Stata code that will be used to analyse the final study data is available on GitHub (16).
- The trial statistician will be blinded to the treatment group until the analyses outlined in this SAP have been completed.
- Changes in the analysis plan by the investigators effective after publication of this SAP will be declared as such.

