#### *Subgroup and sensitivity analyses*

We will undertake two subgroup analyses that were pre-defined in the study protocol:

- age: <six weeks versus  $\geq$ six weeks; and
- physiology: univentricular versus biventricular.

Subgroup analyses will be undertaken using the same analysis methods described for the primary and secondary outcome measures, with the addition of the subgroup variable and its

related interaction term into the main regression model. For each subgroup, the relevant descriptive statistics will be presented for the primary and secondary outcomes, along with the appropriate measure of effect size (and 95% CI) and interaction effect (and 95% CI and p-value). A Forest plot will be developed to present heterogeneity between the treatment group and subgroup variable, including the p-value, and presented as a supplementary figure.

Additionally, a sensitivity analysis for study outcomes will be undertaken including the following variables: treatment group, duration of CPB, surgical complexity (recorded using the risk adjustment for congenital heart surgery [RACHS] score), blood prime using during surgery, sex and strata variables as fixed effects, and site as a random effect. Results will be presented in the same manner as primary analyses and included in the supplementary material.

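### Protocol 11.1 permits post-hoc power to decide whether subgroup results are reliable; power cannot do this, and the SAP's interaction method should cover every reported subgroup instead

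*Combined protocol and SAP*

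**What the plan says.** Protocol 11.1 closes its data analysis paragraph with: "Post-hoc power analyses may be undertaken to determine if results found in sub-group analyses are reliable". It does not say which effect size would enter the calculation or what level of power would count as reliable. The same paragraph makes confidence intervals the main form of presentation for secondary outcomes.

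Protocol 3.3 lists age subgroups at <28, <42 and <90 days, and univentricular against biventricular hearts.

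The SAP (Subgroup and sensitivity analyses) covers two subgroup factors: age below or above six weeks, and physiology. It adds the subgroup variable and its interaction with treatment to the main model. It reports an effect size with 95% CI for each subgroup, together with the "interaction effect (and 95% CI and p-value"). Its list of supplementary material includes the subgroup results and a forest plot, and no power analysis. The SAP neither repeats nor withdraws the protocol sentence.

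**The concern.** Once a subgroup result is in hand, the question is whether it reflects a real difference in treatment effect. Power is a property of a design at an assumed effect. Computed afterwards from the observed effect, it carries no information beyond the p-value. Computed at an effect fixed in advance, it carries no information about the result obtained.

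If the option were used, a significant subgroup result could be presented as confirmed because its observed power looks high, and a null one set aside as underpowered. Both statements would only repeat the p-value. Subgroups have some weight in this trial. Age and physiology are stratification factors, protocol 10.1 lets the monitoring board consider the primary outcome within age subgroups, and the SAP makes no multiplicity correction for secondary or other outcomes.

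**Working it through.** **Inputs.** Significance level: 0.05, two-sided (SAP, Statistical analysis principles: "Statistical tests will be two-sided applying a statistical significance level of 0.05"). Design: "assuming a minimally clinically significant small effect size (0.2 SD), 90% power" (protocol 11.2), with "10% withdrawals, and 15% increase in sample size to account for a non-normal distribution of VFD". Stated size: "1,320 patients (660 per group) would be required". Subgroup sizes are not given, so shares from 10% to 75% of the sample are assumed below.

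**1. The plan's own figure.** Per arm before inflation: n = 2 × (1.960 + 1.282)² / 0.2² = 525.4, rounded up to 526. The total depends on how the 15% and 10% are combined:
- 526 × 1.25 = 657.5, total 1,316
- 526 × 1.15 × 1.10 = 665.4, total 1,332
- 526 × 1.15 / 0.90 = 672.1, total 1,346

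All lie within 3% of 1,320, so the sample size reproduces and is not in question.

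**2. Power at the observed effect.** Let z be the absolute normal deviate for the two-sided p-value. Then

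observed power = Φ(z − 1.96) + Φ(−z − 1.96).

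Only z enters, so only p matters.

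| Two-sided p | z | Observed power |
|---|---|---|
| 0.001 | 3.291 | 90.8% |
| 0.005 | 2.807 | 80.2% |
| 0.01 | 2.576 | 73.1% |
| 0.05 | 1.960 | 50.0% |
| 0.10 | 1.645 | 37.6% |
| 0.20 | 1.282 | 24.9% |
| 0.50 | 0.674 | 10.4% |

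Every significant result therefore shows more than 50% and every non-significant one less.

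**3. Subgroup size drops out.** The standardised effect that gives exactly p = 0.05 is 1.96 × √(2/n). With 50, 132, 330 and 594 per arm this is 0.392, 0.241, 0.153 and 0.114 SD. Observed power is 50.0% in all four cases.

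**4. The same holds for the Mann-Whitney test.** In 900 simulated comparisons of skewed, ventilator-free-day-like data (60, 150 or 300 per arm, about 3% set to zero for death), the rank correlation between the p-value and observed power was −1.00. This is expected, because both come from the same large-sample statistic.

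**5. Power at the design effect of 0.2 SD.** Effective size per arm = 660 × 0.9 / 1.15 = 516.5. For a subgroup with share s,

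power = Φ(0.2 / √(2 / (516.5 s)) − 1.96).

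| Assumed share | Power at 0.2 SD |
|---|---|
| 10% | 17% |
| 20% | 30% |
| 30% | 42% |
| 50% | 62% |
| 75% | 80% |

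The observed result does not appear in the formula. A significant and a null finding in the same subgroup receive the same value.

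**6. Power for the interaction.** For a difference of 0.2 SD between the two subgroup effects, the standard error at a 50:50 split is √(2/258.3 + 2/258.3) = 0.124. Power is Φ(0.2/0.124 − 1.96), about 36%, and it is lower at any other split.

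**The case against.** The strongest case against the point has four parts.

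- **The sentence is only permissive.** It sets no threshold and no decision rule. This stands. A reader might infer that the protocol makes post-hoc power its method for judging subgroups, but the wording does not support that.
- **The protocol never says that the observed effect would be used.** This also stands. The identity with the p-value is exact only on that reading. With 0.2 SD, power does not restate the p-value. One can add that power set in advance affects how often significant findings are true over many tests. That is a reason to state subgroup precision beforehand. It does not separate a true result from a chance one in the same subgroup, so the sentence's stated purpose fails on this reading too.
- **The SAP already does the right thing.** For age at six weeks and for physiology this is correct, and it limits the consequence. It does not reach the <28 and <90 day cuts in protocol 3.3.
- **The harm is speculative.** If 80% power were the bar (the documents give none), a result would need about p = 0.005 to pass, which is stricter than 0.05. This is fair: a reader might infer that chance findings would be certified as reliable, but nothing in the documents makes that happen. Any bar on observed power is nevertheless only a bar on p under another name.

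**Conclusion.** The point holds as a minor one. Protocol 11.1 allows a calculation for a purpose that it cannot serve, whichever effect size is used. Under the observed-effect reading, which is an assumption about what the protocol means, power runs from about 25% at p = 0.20 to 91% at p = 0.001 and adds nothing to p. Under the design-effect reading it varies with subgroup size alone, from 17% at an assumed 10% share to 62% at 50%.

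A reader might go further and conclude that the trial's subgroup inference is unsound. The documents do not support that, because the SAP's subgroup section rests on interaction estimates with confidence intervals and does not call on post-hoc power. What remains is a protocol sentence that the SAP has not withdrawn, and age cuts in protocol 3.3 for which the SAP sets no interaction analysis. The primary analysis, the significance level and the sample size of 1,320 are untouched.

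**What to change.** Delete the sentence from protocol 11.1 and replace it with wording such as: *All subgroup findings, including any age cut in section 3.3 that is reported, will be judged by the treatment-by-subgroup interaction and its 95% confidence interval, using the method in the SAP.* A bare reference to the SAP would not be enough, because its subgroup section names only the six-week cut and physiology.

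If information on subgroup precision is wanted, state the expected subgroup sizes before unblinding, with the confidence interval width or power at 0.2 SD for each subgroup and for the interaction.

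The cost is one sentence. No data, sample size or primary analysis changes.

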### 11.2 SAMPLE SIZE

**Sample Size.** Table 2 reports the pilot data, which supports the sample size calculation. Sample size calculations were updated based on individual patient level data from the pilot study to take the distribution of ventilator free days into account. The pilot study showed an approximate 66 hours (0.33 SD) reduction in ventilator-free days (VFD) associated with the study intervention [26]. Based on the primary outcome measure VFD, 1,320 patients (660 per group) would be required to demonstrate a significant increase in VFD assuming a minimally clinically significant small effect size (0.2 SD), 90% power, two-sided alpha level of significance of 5%, 10% withdrawals, and 15% increase in sample size to account for a non-normal distribution of VFD.

## 12 ETHICS AND DISSEMINATION

### 12.1 Research Ethics Approval

This protocol and the informed consent document and any subsequent modifications will be reviewed and approved by the human research ethics committee (HREC). A letter of protocol approval by HREC will be obtained prior to the commencement of the study, as well as approval for other study documents participant to HREC review. The pilot study received ethical approval by the ethic committee of the Royal Children's Hospital Melbourne (HREC 33112B, RCH Melbourne). Protocol Version 1 has been approved by Children's Health Queensland HREC (HREC/17/QRCH/43).

### 12.2 Modifications to the protocol

This study will be conducted in compliance with the current version of the protocol. Any change to the protocol document or Informed Consent Form that affects the scientific intent, study design, patient

safety, or may affect a participants willingness to continue participation in the study is considered an amendment, and therefore will be written and filed as an amendment to this protocol and/or informed consent form. All such amendments will be submitted to the HREC, for approval prior to becoming effective.

### **12.3 Protocol Deviations**

All protocol deviations must be recorded in the patient record (source document) and on the CRF and must be reported to the PI. Protocol deviations will be assessed for significance by the Principal Investigator. Those deviations deemed to have a potential impact on the integrity of the study results, patient safety or the ethical acceptability of the trial will be reported to the HREC in a timely manner. Where deviations to the protocol identify issues for protocol review, the protocol will be amended as per section 12.2.

### **12.4 Confidentiality**

Participant confidentiality is strictly held in trust by the participating investigators, research staff, and the sponsoring institution and their agents. The study protocol, documentation, data and all other information generated will be held in strict confidence. No information concerning the study or the data will be released to any unauthorised third party, without prior written approval of the sponsoring institution. Clinical information will not be released without written permission of the participant, except as necessary for monitoring by HREC or regulatory agencies.

### **12.5 Dissemination and translation plan**

Given the lead role of the investigators in paediatric intensive medicine their role in regional and state-wide guideline development processes; their involvement in professional colleges and at key educational conferences it is likely that the findings will have nationwide impact across Australia and New Zealand.

Publication in high impact peer-reviewed journals will be sought and presentation at national and international conferences is anticipated. Novel and modern information dissemination strategies will also be used including social media, podcast presentations and Free Open Access Medical education (FOAM) resources to generate discussion and disseminate the outcomes of the study.

1192 *Master consent form and other related documentation given to participants and authorised*  
1193 *surrogates.*

1194

## 13.2 Case Report Forms (CRFs)

## 13.3 Causality and Assessment of Severity – Adverse Events

The severity of an Adverse Event will be assessed as follows:

- **Mild:** Events that require minimal or no treatment and do not interfere with the patient's daily activities.
- **Moderate:** Events that cause sufficient discomfort to interfere with daily activity and/or require a simple dose of medication.
- **Severe:** Events that prevent usual daily activity or require complex treatment.

The relationship of the event to the study drug will be assessed as follows:

- **Unrelated:** There is no association between the intervention and the reported event. AEs in this category do not have a reasonable temporal relationship to exposure to the intervention, or can be explained by a commonly occurring alternative aetiology.
- **Possible:** The event could have caused or contributed to the AE. AEs in this category follow a reasonable temporal sequence from the time of exposure to the intervention and/or follow a known response pattern to the intervention, but could also have been produced by other factors.
- **Probable:** The association of the event with the study seems likely. AEs in this category follow a reasonable temporal sequence from the time of exposure to the intervention and are consistent with the known adverse effects of the treatment, or judgement based on the investigators' clinical experience.
- **Definite:** The AE is a consequence of administration of the intervention. AEs in the category cannot be explained by concurrent illness, progression of disease state or concurrent medication reaction. Such events may be widely documented as having an association with the intervention.

1226

**Study design and participants**

The NITRIC trial is a 1320-patient international, multicentre, randomised, double-blind trial in infants and children less than two years of age undergoing open heart surgery on CPB. A total of 1320 patients will be recruited across the six paediatric cardiac centres in Australia, New Zealand, and The Netherlands. Eligible patients will be randomly assigned to NO at 20 ppm administered into the CPB oxygenator for the entire duration of CPB versus standard care (no NO into the CPB) in a 1:1 ratio with stratification by age (less than six weeks; greater than or equal to six weeks), single ventricle physiology (present or not present) and study site.

The primary hypothesis is to demonstrate that NO during CPB increases VFDs compared with standard care in eligible infants. The full study protocol has been previously published (13) and specified inclusion and exclusion criteria, randomisation and blinding procedures, interventions, study outcomes including primary and secondary outcomes, process of care measures and physiological descriptors, adverse events, safety data monitoring, sample size, and data collection and management.

The study protocol has been approved by the Children's Health Queensland Human Research Ethics Committee (HREC/17/QRCH/43; original submission approved 6th March 2017). Minor modifications to the original study protocol were reviewed and approved by the HREC and are provided in Supplementary Appendix (Section S1). This SAP is based on version 1.4 of the study protocol.

## **Sample size**

Pilot study data demonstrated a 66 hour (0.33 SD) reduction in VFDs associated with the study intervention [26]. Assuming a minimally clinically significant small effect size (0.2 SD), 90% power, two-sided alpha level of significance of 5%, 10% withdrawals, and 15% increase in sample size to account for a non-normal distribution of VFD, 1,320 patients are required (660 per group).

## **Randomisation**

Randomisation is conducted online through the purpose-built REDCap electronic data capture tool hosted at The University of Queensland (14, 15); the randomisation module can only be accessed by the central study coordinator and the site perfusionist, and only after a patient has been screened, is deemed to have met eligibility criteria and has provided informed consent. A randomisation sequence using variable block randomisation with a 1:1 ratio was generated and loaded into REDCap prior to screening of the first patient. Randomisation is stratified on age (<six weeks, ≥six weeks), cardiac physiology (univentricular, biventricular) and study site. The precise time of randomisation occurs variably prior to starting CPB dependent on site logistics, and the intervention begins with start of CPB.

## **Outcome measures**

The definition and detail of calculation of outcome measures can be found in the Supplementary Appendix (Section S2), alongside the Stata scripts written to calculate these outcomes (available on GitHub (16)). Briefly, the outcomes are:

- Primary outcome measure: VFDs within 28 days from start of CPB
- Secondary outcome measures:

- Individual VFD components (i.e. duration of mechanical ventilation, death within 28 days after CPB start)
- Individual and components of composite measure of LCOS, and/or ECLS within 48 hours after CPB start and/or death within 28 days after CPB start;
- Length of PICU stay after CPB start;
- Length of hospital stay after CPB start;
- Process of care measures:
  - Treatment with ECLS within 48 hours after CPB start;
  - Duration of postoperative time spent with open chest including unplanned chest reopening after CPB start;
  - Treatment and duration of treatment using inhalational nitric oxide postoperatively after CPB start;
  - Treatment and duration of treatment of postoperative renal replacement therapy (includes peritoneal and continuous venous-venous haemodialysis) after CPB start;
- Physiological descriptors:
  - Postoperative troponin levels during the first 24 hours postoperatively;
  - Severity and duration of postoperative organ dysfunction; and
  - Postoperative acute kidney injury (AKI) and serum creatinine levels measured during the first 24 hours.

For the purposes of analysis and reporting, LCOS within 48 hours after CPB start, ECLS within 48 hours after CPB start, death within 28 days after CPB start and length of stay in PICU and hospital are classified as potentially patient-important secondary outcomes. The remaining secondary outcomes will be reported to describe patient physiology and processes of care only.

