### *Secondary outcome measures*

For binary outcome measures (e.g. LCOS), logistic regression analyses will be used including age group and physiology as fixed effects, and site as a random effect, with unadjusted and adjusted odds ratios (ORs) and 95% CIs reported (Table 3). Survival outcomes (length of PICU stay, length of hospital stay) will be visually presented using a Kaplan-Meier plot and a Cox proportional hazard model will be used to assess differences between treatment groups with

treatment group and stratification variables as fixed effects and site as a random effect (i.e. utilising a shared frailty model). The hazard ratio and 95% CI will be presented as an estimate of treatment effect. Continuous outcomes (e.g. PELOD-2, duration of renal replacement therapy) will be analysed using linear regression adjusting for age group and physiology as fixed effects, and site as a random effect, with mean difference and 95% CI reported. If the residuals demonstrate non-normality, quantile regression will instead be used in the same manner as for the primary outcome. Key assumptions of the models will be tested and reported on (for logistic regression: specification, goodness-of-fit, absence of multicollinearity and absence of influential observations; for survival analysis: proportionality assumption, goodness-of-fit; for linear regression: specification, distribution of residuals, homoscedasticity, absence of multicollinearity, linearity).

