#### **List of planned figures**

**Figure 1.** CONSORT participant flow diagram

**Figure 2.** Cumulative incidence functions for extubation (accounting for mortality) (all patients, and the pre-specified subgroups)

**Figure 3.** Composite figure of a) bar chart depicting proportion of patients with LCOS, b) mean (and 95% CI) SaO2-ScvO2 difference, c) boxplot of lactate levels, d) boxplot of VIS score, e) mean (and 95% CI) of creatinine values, over time points 0, 6, 12, 24, 48 hours after PICU admission, f) PELOD-2 score at 0, 24, 48 hours after PICU admission, separated by treatment group

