| Outcome                                                               | Standard Care
N= | Nitric
Oxide
N= | Unadjusted
p-value | Estimate of
Difference
(95% CI) | Adjusted
p-value |
|-----------------------------------------------------------------------|---------------------|-----------------------|-----------------------|---------------------------------------|---------------------|
| Primary Outcome                                                |                     |                       |                       |                                       |                     |
| Ventilator-free days median (IQR)                              |                     |                       |                       |                                       |                     |
| Secondary Outcomes                                             |                     |                       |                       |                                       |                     |
| Duration of invasive ventilation median (IQR)                  |                     |                       |                       |                                       |                     |
| Low cardiac output syndrome, need for ECLS or death n (%)      |                     |                       |                       |                                       |                     |
| Low cardiac output syndrome n (%)                              |                     |                       |                       |                                       |                     |
| ECLS n (%)                                                     |                     |                       |                       |                                       |                     |
| Death n (%)                                                    |                     |                       |                       |                                       |                     |
| Length of stay in PICU median (IQR)                            |                     |                       |                       |                                       |                     |
| Length of stay in hospital median (IQR)                        |                     |                       |                       |                                       |                     |

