### 404 *Primary Outcome*

405 The primary outcome of VFD will be calculated as the sum of all episodes of invasive respiratory support, which require an endotracheal tube in situ,  
406 from start of CPB and censored at 28 days after CPB start. Patients who die within this time period will be assigned a value of zero for the VFD outcome.  
407 Ventilated days do not include non-invasive ventilation or high-flow nasal cannulae. Patients who receive a tracheostomy will be counted as ventilated  
408 as long as they receive positive pressure ventilation through the tracheostomy. The individual components of VFDs (duration of invasive respiratory  
409 support from start of CPB within the first 28 days, and death within the first 28 days) will also be presented.

410

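### Duration of invasive ventilation is compared between arms over all randomised children with no rule for deaths, so this exploratory row can understate, miss or reverse a survival effect

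*Combined protocol and SAP*

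**What the plan says.** The SAP, under Outcome measures, names "Individual VFD components (i.e. duration of mechanical ventilation, death within 28 days after CPB start") as secondary outcomes. Table 3 has a row "Duration of invasive ventilation", shown as median (IQR), directly under Secondary Outcomes. Its columns include "Unadjusted p-value", an estimate of difference with 95% CI, and an adjusted p-value.

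Under Datasets analysed, the population is all eligible randomised patients. Under Secondary outcome measures, continuous outcomes go to linear regression, and: "If the residuals demonstrate non-normality, quantile regression will instead be used in the same manner as for the primary outcome".

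Appendix S2 scores VFD as zero for children who die within 28 days. For the components it says only that duration of invasive "support from start of CPB within the first 28 days, and death within the first 28 days) will also be presented". It does not say how a child who dies is counted in the duration. The same appendix does address deaths for length of stay, and it states who is included in the inhaled NO and renal replacement durations.

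Figure 2 is planned as "Cumulative incidence functions for extubation (accounting for mortality"), for all patients and the subgroups. No comparison is attached to it.

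On status, duration of ventilation is not on the SAP's list of potentially patient-important secondary outcomes. Of the others it says: "The remaining secondary outcomes will be reported to describe patient physiology and processes of care only". For secondary results generally, "such results will be considered exploratory and will be reported as point estimates with 95% confidence intervals (CIs").

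**The concern.** Read literally, a child who dies intubated on day 1 contributes about one day of ventilation and ranks better than a survivor ventilated for four days. Protocol section 2.2 hypothesises that NO lowers mortality. If it does, children saved by NO add their full ventilated time to the NO arm, while their counterparts in the control arm add only the time to death. The row and the primary outcome could then point in different directions with no effect of NO on ventilation itself. If NO caused early deaths, the row would show shorter ventilation.

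Readers will look at this row. Aim 1 of the protocol is worded as a reduction in the duration of invasive ventilation, so the row is the natural place to look for an explanation of the VFD result. The subgroup section of the SAP repeats the secondary analyses by age and physiology, including the under-six-weeks group that the protocol describes as carrying the highest surgical risk.

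**Working it through.** The plan gives no figure for this row, so there is none to reproduce. The calculation below sizes the artefact when NO changes mortality only.

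**Inputs from the documents**
- Mortality 2-5% (protocol 2.1).
- Pilot mean ventilation 97.8 h (95% CI 61.5-134.1) in controls and 65.1 h on NO (protocol Table 1, children under 2 years). Difference 97.8 - 65.1 = 32.7 h.
- 660 per group with 10% withdrawals: 660 x 0.9 = 594 per arm.

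**Assumptions (not in the documents)**
- NO halves mortality: 5% v 2.5%, or 2% v 1%.
- All deaths occur on the ventilator, spread evenly over a stated window.
- Saved children are either long-stay cases (7-21 days, mean 336 h) or ordinary survivors (mean 97.8 h).
- Survivor durations are lognormal, and about 66 of the 130 pilot children were controls.

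**Spread.** Control SD = 36.3 / 1.997 x sqrt(66) = 147.7 h. Then sigma^2 = ln(1 + (147.7/97.8)^2) = 1.188, so sigma = 1.090. The median is 97.8 / sqrt(3.281) = 54.0 h. The inverse density at the median is 54.0 x 1.090 x 2.507 = 147.5 h.

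**Formulas (NO minus control).** Let dp be the mortality difference.
- Mean shift = dp x (mean duration of saved children - mean time to death).
- Median shift is approximately dp x (share of deaths before 54.0 h - share of saved children extubated before 54.0 h) x 147.5.

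**Results at 5% v 2.5% (dp = 0.025).** Positive means NO looks worse. Exact medians from the mixture distributions are in brackets.

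| Deaths at | Saved children | Mean shift (h) | Median shift (h) |
|---|---|---|---|
| 12-48 h | 7-21 days | 0.025 x (336 - 30) = +7.65 | 0.025 x 1 x 147.5 = +3.69 (+3.75) |
| 12-48 h | ordinary | 0.025 x (97.8 - 30) = +1.70 | 0.025 x 0.5 x 147.5 = +1.84 (+1.89) |
| 24-144 h | 7-21 days | 0.025 x (336 - 84) = +6.30 | 0.025 x 0.25 x 147.5 = +0.92 (+1.04) |
| 24-144 h | ordinary | 0.025 x (97.8 - 84) = +0.35 | 0.025 x (0.25 - 0.5) x 147.5 = -0.92 (-0.93) |
| 24-336 h | ordinary | 0.025 x (97.8 - 180) = -2.06 | 0.025 x (0.096 - 0.5) x 147.5 = -1.49 (-1.62) |
| 7-21 days | 7-21 days | 0.025 x (336 - 336) = 0 | 0 |
| 7-21 days | ordinary | 0.025 x (97.8 - 336) = -5.96 | 0.025 x (0 - 0.5) x 147.5 = -1.84 (-2.10) |

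With the pilot NO mean in the last row, the mean shift is 0.025 x (65.1 - 336) = -6.8 h, so the lower end is roughly -6.5 h. At 2% v 1% every approximate shift is 0.4 times as large: mean -2.4 to +3.1 h, median about -0.7 to +1.5 h. If NO instead doubled mortality, the signs would flip.

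**Contrast with VFD.** Each saved child moves from 0 to 672 h minus ventilated time. For long-stay cases the gain in mean VFD is 0.025 x (672 - 336) = 8.4 h in favour of NO, including in the rows where duration shows +7.65 h or 0.

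**Chance of p < 0.05 from the artefact alone.** For the median, SE = sqrt(2/594) x 147.5 / 2 = 4.28 h. A shift of 3.75 h gives z = 0.88 and 14%. A shift of 1.04 h gives z = 0.24 and about 6%. At 2% v 1% the chance is 5-6%. For a comparison of means with a pooled SD of about 118 h, SE = 118 x sqrt(2/594) = 6.85 h. Then 6.30 and 7.65 h give 15% and 20%.

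**The case against.** The strongest case against is that nothing rests on this row. It is outside the patient-important list, secondary results are exploratory, and the row only decomposes a primary outcome that already scores death as zero. VFD and death stand in the same table, and Figure 2 accounts for mortality. A reader who saw shorter ventilation with more deaths would see both together. The outcome-calculation code that the SAP cites is outside the documents and may contain a rule. All of this stands, and it is why the point is minor. None of it supplies a death rule in the written plan, and an estimate with p-values will be read even when labelled exploratory.

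Three stronger readings are tempting, and the documents do not support them:
- A reader might infer that the sign is always wrong. It is wrong only when deaths come earlier than the ventilation those children would otherwise have had. With deaths at 7-21 days and ordinary survivors, the sign is right.
- A reader might take the shift of 7-8 h as typical. It needs mortality at the top of the 2-5% range, deaths within 48 h, and saved children ventilated 7-21 days. With ordinary survivors it falls to +1.70 h. The documents give neither the timing of deaths nor the ventilation of saved children.
- A reader might apply the 15-20% rejection rates. Those are for means. The row is a median, and skewed residuals would send the analysis to quantile regression, where the most extreme scenario gives about 14% and the others stay closer to 5%.

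**Conclusion.** The gap is real but small. As written, Table 3 compares a duration that is cut short by death, with an estimate and p-values, and S2 gives no rule for children who die. The row can understate, miss or reverse a survival effect. At 2-5% mortality halved by NO, the artefact is roughly -2 to +4 h in the median and -6.5 to +8 h in the mean, against a pilot mean difference of 32.7 h. It is unlikely to produce a finding alone.

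The range rests on assumed lognormal durations, death times and ventilation of saved children. It scales with the mortality difference. The primary outcome, the sample size and the death row are unaffected. Severity: minor.

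**What to change.** In S2 and Table 3, make the between-arm comparison for this component time to final extubation within 28 days of CPB start, with death as a competing event. This matches what Figure 2 plots. Report an estimate adjusted for the strata and site, with 95% CI. Differences in cumulative incidence at landmark days are optional.

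Keep median (IQR) ventilated time as a descriptive row, split by alive or dead at day 28, without a difference or p-value.

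The cost is a few sentences of SAP wording and slightly more analysis code, with no new data. The downside is that the table loses a directly readable difference in hours of ventilation. Because the SAP is already published, the change should be declared as its own principles require.
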